#### Telephone support plus anticipated regret only (TEL-SUPP-AR)

In the TEL-SUPP-AR group, participants will receive exactly the same intervention as the TEL-SUPP condition, with the addition of two questions relating to Anticipated Regret, ‘If you didn’t make another appointment to attend for breast screening, would you later wish you had?’; ‘If you didn’t attend for breast screening, would you later regret it?’ Participants would be asked to respond ‘Yes’, ‘No’, ‘Maybe’ or ‘Don’t know’. These questions would be asked at the end of the support intervention, immediately before the question relating to intention to attend screening.

### Training materials

Detailed training materials will be produced by the Research Fellow, based on the techniques and materials used in the telephone intervention. This will enable the intervention to be subsequently conducted by NHS staff.

### Sampling and randomisation

Participants will be selected from those receiving an appointment for breast screening who do not telephone to cancel their appointment and who fail to attend or to re-arrange their appointment before the reminder letter is due to be sent. Sampling will be from the lists of women for whom reminder letters are generated. Postcodes will be used to derive Scottish Index of Multiple Deprivation (SIMD) vigintiles, and women who are from a SIMD vigintile between 1 and 12 inclusive (where 1 represents the most deprived areas), for whom telephone numbers can be obtained, will be randomised to treatment arm in a 1:1:1:1 ratio.

In order to achieve a balance between treatment groups, randomisation will be carried out by a member of the research team who is independent of the intervention on a record by record basis using minimisation via the MINIM software program [20] with age band (50–56, 57–63, 64 or older) and SIMD quintiles (i.e. 1, 2, 3 equivalent to vigintiles 1–4, 5–8 and 9–12) as the minimisation variables. The minimisation algorithm allocates the first record randomly and subsequent participants are allocated to minimise the imbalance between groups on the minimisation variables. It is currently the best available method of achieving randomisation whilst “ensuring excellent balance between groups for several prognostic factors, even in small samples” [21]. To ensure that the researcher does not influence the randomisation process, participants will be entered into the MINIM software sequentially, according to their order in the reminder letter list and the researcher will also remain blind to the identity of each treatment group (i.e. by randomising only to A, B, C, or D) during the randomisation process. The same researcher will collect the three-month follow-up data and carry out the data analysis and will continue to remain blind to the identity of each treatment group until this is complete.

### Data collection and security

The Research Fellow will require access to patients' personal details to enable contact by telephone. Only the minimum information required for contact will be recorded. Any personal information will be stored separately from data collected at interview. All information will be kept either on a secure network computer and/or in a locked filing cabinet, in a locked office, at the University of Stirling.

A unique anonymised identifier will be used to enable matching with the follow-up attendance data. The follow-up attendance data will be collected from the screening database on-site at the Breast Screening Centre, 3 months after the reminder intervention. The anonymised data from the telephone interventions and attendance screening data will be stored on a secure password-protected network server computer and analysed by the Research Fellow at the University of Stirling. Data integrity will be enforced by cross-checking with the recorded interview after the intervention is complete and by valid value and range checks at the time of data entry. Data storage systems at the University are built to be resilient to failure; their locations have secure physical entry and protected power supplies and are guarded by fire and intruder alarms. Data will be kept for a period of 10 years, in line with University Policy, after which it will be securely destroyed.

### Primary and secondary outcomes

The primary outcomes, collected at 3-month follow-up, will be whether or not each patient makes another appointment for breast screening and whether or not they attended screening within 3 months of receiving their reminder (letter or telephone call). Previous attendances and previous failures to attend (attendance history) will also be collected at this time. Secondary measures for the two telephone support arms, collected during the telephone interview, are intention to make another appointment, anticipated regret, number of barriers to breast screening mentioned by participants, and specific barriers reported. In addition the percentage of participants for whom telephone numbers are obtainable at the outset is an important secondary outcome.

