**Methods/Design:**

We will employ a brief telephone reminder and support intervention, whose purpose is to elicit and address any mistaken beliefs women have about breast screening, with the aim that the perceived benefits of screening come to outweigh any perceived barriers for individuals. We will test whether this intervention, plus a simple anticipated regret manipulation, will lead to an increase in the uptake of breast cancer screening amongst low-income women who have failed to attend a first appointment, in a randomised controlled trial with 600 women. Participants will be randomly allocated to one of four treatment arms i.e. 1) Letter reminder (i.e. Treatment as usual: CONTROL); 2) Telephone reminder (TEL), 3) Telephone reminder plus telephone support (TEL-SUPP) and 4) Telephone reminder plus support plus AR (TEL-SUPP-AR). The primary outcome will be attendance at breast screening within 3 months of the reminder letter.

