#### Letter reminder group (CONTROL)

Participants randomised to the Control group will receive the reminder letter only, as current practice. This will be sent from the East of Scotland Breast Screening Centre.

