#### All telephone groups (TEL, TEL-SUPP, TEL-SUPP-AR)

All telephone groups will receive the standard reminder letter in the same manner as the Control group. Participants in each of the three telephone groups will also be telephoned by the Research Fellow from the University of Stirling within two weeks of the reminder letter being posted. Telephone calls will be tape-recorded in order to check the fidelity of the intervention, and also to ensure accuracy of the participant’s answers recorded on the check-list. Participants who opt not to allow their calls to be recorded will still be able to take part in the intervention. Participants who do not answer or are not at home when telephoned, would be called on a maximum of 5 occasions, after which they would be recorded as non-contactable.

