### Analysis

Our primary analysis will be chi-square to detect differences in the proportion of respondents who attended breast screening within 3 months of the reminder letter or call as a function of the 4 arms (control, TEL, TEL-SUPP or TEL-SUPP-AR). This will be followed by logistic regression of attenders versus non-attenders in the four groups, controlling for potential between-arm differences in age, social deprivation (SIMD) and history of previous breast screening attendance. Our primary analysis will be on an ‘Analysed as Allocated’ basis, i.e. including all participants, whether or not they were successfully contacted by telephone and/or agreed to take part in the study. Secondary analysis will be conducted for those agreeing to and participating in the intervention (TEL-SUPP and TEL-SUPP-AR groups only) to test the mediating and moderating roles of reported barriers, intention and AR in uptake of screening after reminder.

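### The start of the primary endpoint's 3-month window is stated inconsistently, and one permitted reading gives women reached by telephone up to 14 more days than Control

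*Protocol article*

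**What the plan says.** The protocol article describes the endpoint's time origin in four places.

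- **Abstract, Methods/Design:** "The primary outcome will be attendance at breast screening within 3 months of the reminder letter". Only the letter is named.
- **Primary and secondary outcomes:** "whether or not they attended screening within 3 months of receiving their reminder (letter or telephone call". Either event may be the origin.
- **Analysis**, where the primary chi-square test is set out: "attended breast screening within 3 months of the reminder letter or call as a function of the 4 arms". Again either event, with no statement of which applies to whom.
- **Data collection and security:** follow-up data are extracted "3 months after the reminder intervention". This is an extraction time, and the event is not defined by arm.

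Two sections describe what each arm receives. For Control: "Participants randomised to the Control group will receive the reminder letter only, as current practice". For the other three arms: "All telephone groups will receive the standard reminder letter in the same manner as the Control group". Women in those arms are also "telephoned by the Research Fellow from the University of Stirling within two weeks of the reminder letter being posted". After five unsuccessful attempts a woman is recorded as non-contactable, but the Analysis section keeps her in the primary comparison.

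**The concern.** Control has only one possible origin, the letter. The telephone arms have two, and the call comes later. An analyst following the abstract and one following the outcomes section could classify the same woman differently if she attended between day 91 and day 105 after her letter.

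If the call is the origin, three things follow.

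1. Women reached by telephone are observed for longer after the letter than Control women. This bears on the second research question, whether the telephone intervention increases uptake, and it acts in the direction of the hypothesis. Analysis as allocated and covariate adjustment do not correct unequal observation time.
2. Women in the same arms who are never reached have no call date, so the window also differs within an arm.
3. Sampling and randomisation says that the person who collects the 3-month data and analyses them stays blind to the identity of each group. Cut-off dates that depend on calls would tend to show that person which women had been telephoned.

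**Working it through.** The plan gives no figure for the length of the window by arm, so there is nothing to reproduce. The check has two steps.

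**Step 1: window measured from the letter.** Take 3 months as 13 weeks = 91 days. The lag from letter to call is 0 to 14 days (section on all telephone groups).

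- Control: 91 days.
- Telephone arms, woman counted from her call: 91 + 0 to 91 + 14 = 91 to 105 days, at most 14/91 = 15% longer.
- Telephone arms, woman never reached: 91 days.

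**Step 2: spurious difference with no true effect.** From the documents: 150 women per arm (600 allocated 1:1:1:1), a planning attendance rate of 69%, and planned gains of 3 points (TEL) and 11 points (support arms). Assumed, because the documents do not give them:

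- 3-month attendance r of 10%, 20%, 30%, 50% or 69%. Endnote b gives 69% as national attendance in vigintiles 1–12, whereas this trial enrols women who missed an appointment, so lower rates are also tried.
- Proportion reached c of 50% or 100%.
- Extra time e of 1 or 2 weeks for each woman reached.

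*Constant hazard:* λ = −ln(1 − r)/13 per week; gain = c × {[1 − exp(−λ(13 + e))] − r}.

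*Early attendance:* attendance times fall off with a 3-week half-life, h = ln 2/3, A = r/(1 − exp(−13h)); gain = c × {A[1 − exp(−h(13 + e))] − r}.

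Example with r = 69%, c = 100%, e = 2:

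- Constant hazard: 1 − 0.31^(15/13) = 74.1%, a gain of 5.1 points.
- Early attendance: 0.69 × (1 − 2^(−15/3))/(1 − 2^(−13/3)) = 0.69 × 0.9688/0.9504 = 70.3%, a gain of 1.3 points.

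The last two columns give the chance that the planned 4-arm chi-square test (3 df, nominal 5%, noncentral chi-square) rejects when all three telephone arms carry the gain and there is no true effect.

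| r | c | e (weeks) | Gain, constant hazard (points) | Gain, early attendance (points) | Rejection, constant hazard | Rejection, early attendance |
|---|---|---|---|---|---|---|
| 10% | 50% | 1 | 0.4 | 0.05 | 5.1% | 5.0% |
| 30% | 50% | 1 | 1.0 | 0.2 | 5.3% | 5.0% |
| 30% | 100% | 2 | 3.7 | 0.6 | 9.5% | 5.1% |
| 50% | 100% | 2 | 5.1 | 1.0 | 12.7% | 5.2% |
| 69% | 50% | 1 | 1.3 | 0.4 | 5.6% | 5.0% |
| 69% | 100% | 2 | 5.1 | 1.3 | 15.2% | 5.6% |

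Over all combinations tried, the gain is 0.4 to 5.1 points under a constant hazard (rejection 5.1% to 15.2%) and 0.05 to 1.3 points with early attendance (rejection 5.0% to 5.6%). Between the rates tried, the constant-hazard maximum is marginally higher: at r = 60%, 1 − 0.40^(15/13) = 65.3%, a gain of 5.3 points.

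**A middle case.** With r = 25% and a constant hazard, a full 14 days gives 1 − 0.75^(105/91) = 28.2%, or +3.2 points. If the mean extra time is 7 days (calls spread evenly over the two weeks), 1 − 0.75^(98/91) = 26.6%, or +1.6 points. If in addition 60% are reached, the gain is 0.6 × 1.6 = 1.0 point.

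**With one origin for all arms,** the extra time is 0 days, the spurious difference is 0 points and the test returns to its nominal 5%.

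**The case against.** The strongest reply is that unequal windows are only one reading. Neither the outcomes section nor the Analysis section says that Control is counted from the letter and the telephone arms from the call. Every arm gets the letter in the same way, so a letter origin throughout agrees with the abstract and is compatible with the looser wording elsewhere. The Informed consent section wants calls made close to posting so that timing is comparable across groups, which makes 14 days a ceiling and not a typical lag. Blind outcome collection also fits a common origin better. On size, the larger figures need nearly every woman reached, calls at the end of the two weeks and a constant hazard, none of which is documented.

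Most of this stands. A reader might infer that the plan gives the telephone arms a longer window, or that their uptake will be inflated by about the 3 points assumed for TEL. The documents support neither inference: the first picks one of several conflicting statements, and the second takes near-extreme assumptions as typical. Nor does the data-collection section license the call as origin, since it names neither letter nor call.

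The inconsistency itself is not answered. Parity in when calls are made does not set a common start for the endpoint, and the section that defines the primary test admits the call. Two weeks is also not a firm limit for every woman: Informed consent allows call-backs and a further call after the information sheet is posted, and nothing says which call would count.

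**Conclusion.** The primary endpoint's time origin is stated inconsistently and needs to be reconciled; that much rests on the text alone. Bias is conditional on the call being used as origin in the telephone arms. It would then favour those arms over Control, and would largely spare comparisons among the telephone arms, including the question of what anticipated regret adds.

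Its size cannot be determined from the documents. It runs from negligible (about 0.05 to 1.3 points if attendance comes early) to material (0.4 to 5.1 points under a constant hazard at the rates tried). The 5.1 points at the planning rate of 69% needs all women reached and a full two-week lag. With calls spread over the fortnight and partial contact, about 1 point is a reasonable illustration. If the abstract's letter-only origin governs, there is no bias.

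**What to change.** In the abstract and in the sections on data collection, outcomes and analysis, use one definition: attendance, by the date in the screening database, within a fixed number of days (for example 91) of the posting date of the reminder letter. Apply it identically in all four arms, whether or not the woman was reached by telephone. Extract each woman's data only after her cut-off date has passed, and work from letter dates alone so that call dates need not reach the blinded outcome collector.

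The cost is wording. All arms receive the letter and attendance already comes from the screening database, so no extra women or data are needed. The one drawback is that telephone-arm women have up to 14 fewer days of credited follow-up after the call than under a call-based window.

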### Analysis

Our primary analysis will be chi-square to detect differences in the proportion of respondents who attended breast screening within 3 months of the reminder letter or call as a function of the 4 arms (control, TEL, TEL-SUPP or TEL-SUPP-AR). This will be followed by logistic regression of attenders versus non-attenders in the four groups, controlling for potential between-arm differences in age, social deprivation (SIMD) and history of previous breast screening attendance. Our primary analysis will be on an ‘Analysed as Allocated’ basis, i.e. including all participants, whether or not they were successfully contacted by telephone and/or agreed to take part in the study. Secondary analysis will be conducted for those agreeing to and participating in the intervention (TEL-SUPP and TEL-SUPP-AR groups only) to test the mediating and moderating roles of reported barriers, intention and AR in uptake of screening after reminder.

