### Research questions

Is a simple, telephone reminder intervention, aimed at eliciting and addressing the barriers and concerns of women in socially-deprived areas regarding attending screening at the East of Scotland Breast Screening Service, feasible and acceptable to participants?Can this brief, telephone intervention increase uptake in non-attenders from socially-deprived areas?Does adding anticipated regret to the telephone intervention have any additional benefit in terms of increasing uptake of screening in non-attenders?

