### Power calculations

A power calculation indicates that a sample of 600 participants would provide 80% power (at the 5% level) of detecting an increase of 11% in the TEL-SUPP and TEL-SUPP-AR groups versus no increase in the Control group and a 3% increase in the telephone reminder group (TEL), assuming a base attendance rate of around 69% (as currently present in vigintiles 1–12). This would also equate to 67% power (at 5% level) of detecting an increase in uptake of 9% spread across the 3 telephone intervention arms versus the Control group.

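### The analysis labelled primary is an unadjusted four-arm chi-square with no named contrast, so on its own it cannot show whether telephone support raises uptake or whether anticipated regret adds to it

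*Protocol article*

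**What the plan says.** All references are to the protocol article.

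- **Research questions.** After feasibility, the second question is "Can this brief, telephone intervention increase uptake in non-attenders from socially-deprived areas" and the third is "Does adding anticipated regret to the telephone intervention have any additional benefit in terms of increasing uptake of screening in non-attenders".
- **Analysis.** The primary test is set out thus: "Our primary analysis will be chi-square to detect differences in the proportion of respondents who attended breast screening". Attendance is judged at three months, and the comparison is made "as a function of the 4 arms (control, TEL, TEL-SUPP or TEL-SUPP-AR"). The regression sentence comes next: "This will be followed by logistic regression of attenders versus non-attenders in the four groups, controlling for potential between-arm differences in age, social deprivation (SIMD"). Prior screening attendance is a further covariate in that model. Neither sentence names a comparison between particular arms.
- **Sampling and randomisation.** Women "will be randomised to treatment arm in a 1:1:1:1 ratio", by minimisation "with age band (50–56, 57–63, 64 or older) and SIMD quintiles".
- **Power calculations.** With 600 women, 80% power is claimed for "an increase of 11% in the TEL-SUPP and TEL-SUPP-AR groups", with no increase in Control, 3% in TEL and a base rate of about 69%. A second statement gives 67% power for a 9% increase across the three telephone arms.
- **Primary and secondary outcomes.** Two primary outcomes are listed: making another appointment, and attending.

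**The concern.** A significant 2×4 chi-square says only that the four attendance rates are not all equal. It does not say which arm differs or in which direction. The second and third research questions each call for a specific 1-df comparison: the support intervention against a comparator, and TEL-SUPP-AR against TEL-SUPP. The test that carries the primary label supplies neither.

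Three things are at stake. A positive primary result could be read as evidence for support or for AR when it is evidence for neither. Power is spread over three degrees of freedom when the questions need one at a time. And because the power scenario gives both support arms the same increase, the AR question has no planned effect, so a null AR result would say little. The Discussion nevertheless looks ahead to national implementation if the AR arm shows a clear advantage.

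**Working it through.** **Inputs.** 600 women allocated 1:1:1:1, so 150 per arm. Base rate 69%, with increases of 0, 3, 11 and 11, read as absolute points. The 5% level is taken as two-sided, because the article does not say.

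**1. The stated 80%, using the stated primary test.** The noncentrality is λ = n Σ(pᵢ − p̄)² / [p̄(1 − p̄)].
- Rates 0.69, 0.72, 0.80, 0.80 give p̄ = 0.7525 and Σ(pᵢ − p̄)² = 0.009475.
- λ = 150 × 0.009475 / (0.7525 × 0.2475) = 7.63.
- Against the 3-df critical value of 7.81, power is **63%** (63% in 200,000 simulated trials). Reaching 80% needs about 215 per arm, or 860 women.

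The 80% is therefore not reproduced by the omnibus test. Of the variants tried, only two came within 2 points: a 1-df contrast with scores 0, 3, 11, 11 (79%), and a one-sided test of pooled support versus Control (82%).

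**2. The second power statement.** Rates 0.69, 0.78, 0.78, 0.78 give p̄ = 0.7575, Σ(pᵢ − p̄)² = 0.006075, λ = 4.96 and power **44%**, against the stated 67%. Pooled telephone arms versus Control give 60% two-sided and 71% one-sided, so neither reproduces 67%.

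**3. What a rejection would mean.** In the first scenario the omnibus test rejects 63% of the time although AR adds nothing. In the second it rejects 44% of the time although neither support nor AR adds anything to the reminder call.

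**4. Comparisons that bear on the questions.** Power = Φ{(|p₂ − p₁| − 1.96·SE₀)/SE₁}, with SE₀ from the pooled rate and SE₁ from the separate rates.

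| Comparison | Rates | n | Power |
|---|---|---|---|
| Pooled support v Control | 80 v 69% | 300 v 150 | 73% |
| TEL-SUPP v Control | 80 v 69% | 150 v 150 | 59% |
| Pooled support v TEL | 80 v 72% | 300 v 150 | 48% |
| TEL-SUPP-AR v TEL-SUPP | 80 v 80% | 150 v 150 | no planned difference |

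For the first row: SE₀ = √[0.7633 × 0.2367 × (1/150 + 1/300)] = 0.0425, SE₁ = 0.0443, and Φ[(0.11 − 0.0833)/0.0443] = 0.73.

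**5. Detectable AR difference.** The increments here are assumptions. Over a base of 80%, 150 v 150 gives 21% power for +5 points, 68% for +10 and 80% for about **+11** (0.113).

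**The case against.** The strongest reply is that the plan as a whole does more than its primary test. The sentence after the chi-square adjusts for age, SIMD and attendance history, so a reader who infers that the plan ignores its minimisation factors is mistaken; only the test labelled primary omits them. A four-group logistic model also yields arm-specific odds ratios with a direction, so the stronger inference that the trial cannot answer its second and third questions at all is not supported. An omnibus test followed by a model is conventional, and contrast coding may sit in an analysis plan that is not shown. All of this stands. What remains is that this article fixes the primary label on a test that answers neither question.

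A reader might also infer that omitting the minimisation factors costs material precision. The article gives no figures from which to quantify this. As an illustration only, assumed attendance of 63/69/75% across the three SIMD strata explains about 1.1% of outcome variance and lifts omnibus power from 63.1% to about 63.7%; 60/69/78% lifts it to about 64.4%. The effects of age and history are not given.

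Pooled support versus Control has its own limit: it mixes the reminder call with the support content. Under the second power scenario it rejects about 55% of the time although support adds nothing to the call. It must therefore be described as a package effect, with support versus TEL reported beside it.

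Finally, this is a pilot with feasibility as its first question, and reordering the tests does not raise power for AR. That is correct. It is a reason to state the detectable difference, and it leaves the case for naming the contrasts intact.

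**Conclusion.** The point holds in a limited form. The primary test, taken alone, does not answer the second or third research question, and the adjusted model that could do so is neither primary nor tied to a contrast. On the protocol's own rates the omnibus test has about 63% power, against 73% for pooled support versus Control. The AR comparison has no assumed effect and could detect only about 11 points above 80%. These figures assume exactly 150 women per arm, a two-sided 5% level, increases in absolute points and the stated 69% base. The gain from covariate adjustment is probably modest and is not part of the case. This is a worthwhile improvement to the plan; the planned analysis is not invalid.

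**What to change.** 1. Make the planned logistic regression the primary analysis for attendance. Enter age band and SIMD quintile as used in the minimisation, and restrict attendance history to events before randomisation, because it is collected at the three-month follow-up.
2. Test two ordered 1-df contrasts at 5%: first TEL-SUPP and TEL-SUPP-AR pooled versus Control, described as the effect of call plus support; then, only if that is significant, TEL-SUPP-AR versus TEL-SUPP.
3. Report each as a risk difference with a 95% confidence interval.
4. Report pooled support versus TEL as the key secondary comparison, since it isolates the support content. Keep the omnibus test and TEL versus Control as secondary.
5. State the detectable AR difference.
6. The ordering holds familywise error at 5% for attendance only. Making an appointment is also listed as primary, so make it secondary or give it a place in the order.

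The cost is wording only: no new data, women or procedures. The downsides are that the omnibus test and TEL versus Control lose primary status, and that AR is tested formally only if the first contrast succeeds (73% power on the protocol's rates).
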